### Design

The proposed study concerns a prospective multi-centre randomised controlled trial with one experimental and one control group. The starting point is a superiority design with the research hypothesis that Australian Medical Sheepskins are a better pressure relieving device than usual care; that they will reduce the incidence rates of sacral pressure ulcers; and will also reduce costs involving pressure ulcer treatment.

Data will be gathered primarily in an empirical way and additionally through systematic literature searches with regard to the cost-effectiveness question.

For assessing the cost-effectiveness, the Australian Medical Sheepskin will be compared only to usual care and not to other pressure relieving materials. The perspective of the health care organisation will be considered to measure the cost-effectiveness.

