### Intervention

The experimental condition consists of the application of the Australian Medical Sheepskin as an overlay on top of the standard/usual mattress in the area of the buttocks and in the (wheel)chair, combined with all care as usual. An extra Australian Medical Sheepskin at the bottom of the bed is also permitted. The intervention will start no later than 48 hours after admission. The Australian Medical Sheepskin will be applied during the first 30 days after admission (and prolonged if the patients wish so, but without gathering research data). The period of 30 days is chosen because most pressure ulcers develop in the first weeks after admission [6,10,36,37]. The sheepskins will be changed at least every two days.

Besides the use of the Australian Medical Sheepskin, all other usual pressure ulcer preventative interventions such as mobilization and repositioning may be added as co-interventions, in so far as they are normally used in the participating nursing homes. All other nursing care can be continued as usual (including incontinence materials).

The control group will receive usual care, including all the pressure relieving interventions and other preventive actions, normally taken in the participating nursing homes. The application, in any way, of the Australian Medical Sheepskin is forbidden in this group.

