### Outcomes

A distinction can be made between variables relating to the effectiveness (incidence, prevalence of pressure ulcers) and variables relating to costs (purchase and washing of the sheepskins on the one hand, and investment of time and materials cost for pressure ulcer treatment on the other). Both of these are necessary to compute cost-effectiveness.

The primary outcomes for this study are:

- the incidence of sacral pressure ulcers in the first 30 days after admissions,

- the costs of appliance of the sheepskin, and

- the costs related to treatment of the pressure ulcers that have developed.

Secondary outcomes are the presence of pressure ulcers on other places, quality of life, comfort of the sheepskin as experienced by the patients and ease of use of the sheepskin as experienced by the care personnel.

Influencing factors that will be measured are patient characteristics, the application of other pressure relieving interventions and materials and the use of incontinence materials.

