### Instruments

These outcomes, as well as influencing factors, will be measured by appropriate instruments, as far as possible we will use already existing and validated instruments. The EPUAP grading system is used to assess the presence and severity of pressure ulcers [38].

To this end a 'daily observation checklist' has been developed. Nurses use this checklist during the first 30 days after admission to report the presence/absence of sacral pressure ulcers, as well as the ulcer grade; the presence/absence of pressure ulcers on other locations and whether a sheepskin, repositioning, other support surfaces and incontinence material are applied.

When nurses feel uncertain about their observations they are instructed to call another specialized nurse, experienced in observing pressure ulcers.

Furthermore, a photographic series of the various pressure ulcer grades is available on each ward, as well as special glasses that can be used in order to differentiate better between blanchable and non-blanchable erythema. Finally, all nursing homes are offered a lesson in pressure ulcer observation.

The daily skin observations by nurses during routine care will be checked weekly by an experienced nurse observator from the nursing home itself and bimonthly by the principal investigator from the central research office.

Influencing patient factors that will be measured are age, gender, principal medical diagnosis category, surgery in the last month, presence of pressure ulcers at admission on other places than the sacrum, incontinence status, nutritional status (including body mass index), activity of daily living level (Barthel-index) and pressure ulcer risk score (Braden-scale). These are measured twice: at admission and at day 30 after it.

Furthermore the patients in the sheepskin group are asked at the end of the research period to rate the (dis)comfort of the sheepskin. For this purpose, a self-developed 7-item questionnaire with a 5-point rating answer structure was developed.

Data about costs that will be gathered are the costs of buying sheepskins, costs of washing sheepskins, costs of treatment of pressure ulcers (medication, wound care materials, diagnostics, kind of specialized consultants and time involved, and extra time for nurses/carers with regard to pressure ulcer treatment).

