## Discussion

This study is innovative because it is the first to assess the cost-effectiveness of the Australian Medical Sheepskin in nursing home patients and also because current opinions and guidelines [13,41-44] oppose the use of sheepskins. However, these are based on old forms of sheepskins, not comparable to the genuine Australian Medical Sheepskin.

A difficult point in this research is that the usual care can not be standardized. Although nurses and nursing homes may have pressure ulcer protocols and say that they are following these, there is a chance that the usual care differs from nursing home to nursing home, or even from nursing ward to nursing ward, and that individual nurses may deviate from the protocol. Moreover, it is known that different mattresses are in use in and between nursing homes. Since standardization is in no way possible, a registration of mattresses and devices applied will be conducted.

With regard to possible contamination between experimental and control group, the following measures will be taken: clear instruction to all nursing and care personnel and patients, a limited stock of sheepskin on the ward, daily inspection of the skin by the research team in both groups, and a concise control and observation to ascertain whether the patients are still being nursed in the condition they were randomized to. Moreover it is not very likely that patients from both groups will be nursed on the same room during the same period (1.2 admissions per bed); therefore it is improbable that patients from the control group will ask for a sheepskin.

Finally, in the information sessions with nurses, it will be stressed that the Australian Medical Sheepskin is NOT a replacement for the normal pressure relieving interventions such as repositioning and other methods.

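### The stated cost items leave out nursing time to fit and change sheepskins, which understates the incremental cost in the sheepskin's favour

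*Protocol article*

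**What the plan says.** All references are to the protocol article.

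- **Perspective and comparator (Design).** "The perspective of the health care organisation will be considered to measure the cost-effectiveness". The same section adds that "the Australian Medical Sheepskin will be compared only to usual care and not to other pressure relieving materials".
- **Cost variables (Outcomes).** These are described as "purchase and washing of the sheepskins on the one hand, and investment of time and materials cost for pressure ulcer treatment on the other". Two of the three primary outcomes are costs: one for applying the sheepskin and one for treating ulcers that develop.
- **Data to be collected (Instruments).** "Data about costs that will be gathered are the costs of buying sheepskins, costs of washing sheepskins, costs of treatment of pressure ulcers". The detail in parentheses covers treatment only, and its nursing item is "extra time for nurses/carers with regard to pressure ulcer treatment". Of the five data forms listed, the one about cost concerns ulcer therapy.
- **Workload created by the intervention (Intervention).** "The sheepskins will be changed at least every two days", over the first 30 days after admission. Sheepskin goes on the bed and in the (wheel)chair, and an extra one at the foot of the bed is allowed.
- **Other prevention (Instruments, Outcomes, Discussion).** The daily checklist records whether repositioning, other support surfaces and incontinence material are applied, and mattresses and devices are registered. Other pressure-relieving measures and incontinence materials are named as influencing factors. No costing of them is stated.

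**The concern.** The same resource, nurse time, is priced where an effective sheepskin would save it (fewer ulcers to treat) and not where the sheepskin uses it (fitting and changing). Under the stated perspective the nursing home bears both. An incremental cost built from the listed items therefore credits the sheepskin with staff savings and leaves out part of its staff cost.

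This bears on research question 4, cost-effectiveness against usual care. It also bears on the economic model described under Data-analysis, which is meant to show consequences for an average nursing home and/or nationally and would carry the omission to that scale.

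A second, weaker issue concerns other prevention. It makes up the comparator and is allowed alongside the sheepskin, but no price is attached to it in either arm.

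**Working it through.** The protocol gives no unit price, wage or time per change, so there is no cost figure of its own to reproduce. What can be derived is the number of uncosted changes.

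**Inputs from the protocol**
- Minimum change frequency: every 2 days (Intervention).
- Period of application: first 30 days after admission, starting within 48 hours (Intervention).
- Assumed incidence: 28% control, 18% sheepskin (Sample size calculation).
- Planned arm size: 375 (Sample size calculation).

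**Input not in the protocol**
- Minutes per change: assumed 1 to 10.

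**Step 1. Changes per patient, one skin location**
30 / 2 = 15. With a start at 48 hours, (30 − 2) / 2 = 14.

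**Step 2. Patients treated per ulcer averted**
1 / (0.28 − 0.18) = 10.

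**Step 3. Changes per ulcer averted**
10 × 15 = 150. If all 375 patients completed the period, the arm total would be 375 × 15 = 5,625.

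**Step 4. Uncosted nurse time, one location**

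Hours per patient = 15 × minutes / 60. Hours per ulcer averted = 150 × minutes / 60.

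| Assumed minutes per change | Hours per patient | Hours per ulcer averted |
|---|---|---|
| 1 | 0.25 | 2.5 |
| 2 | 0.5 | 5 |
| 5 | 1.25 | 12.5 |
| 10 | 2.5 | 25 |

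**Step 5. What moves these figures**
- Two skins (bed and chair) changed each time doubles the last column: 5 to 50 hours.
- Shorter use lowers it. If mean use were 15 days (an assumption), then 10 × 15 / 2 = 75 changes per ulcer averted, or 75 × 1 / 60 = 1.25 to 75 × 10 / 60 = 12.5 hours.
- The sign does not change. Controls may not use the sheepskin, so their change time is zero. Any positive extra time per change raises the incremental cost.

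**Step 6. Other prevention**
Its contribution to the incremental cost is unit cost × (mean use in the sheepskin arm − mean use in the control arm). This is zero if use is equal. Otherwise it takes the sign of the difference, which the protocol does not allow one to predict.

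**The case against.** **Condensed article.** Unit prices and the handling of co-interventions commonly sit in a full protocol or economic plan that is not shown. This stands for the costing of other prevention, where the article is merely silent. It is weak for change time: Outcomes and Instruments give matching lists of what will be costed, and Instruments names nurse time for treatment only.

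**Broader wording.** The primary outcome is phrased as "the costs of appliance of the sheepskin, and", which could be taken to include staff time. The two fuller lists spell it out as purchase and washing, so this reading has little support.

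**Other prevention may cancel.** Allocation is randomised, and the same usual prevention is allowed in both arms. Use is recorded daily, and the analyses are to be controlled for influencing factors. This stands: no bias from this source is shown, only the possibility of one in unblinded, unstandardised care.

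**Reading too much into the instruction to nurses.** A reader might infer that the authors expect substitution, because information sessions will stress that the sheepskin is "NOT a replacement for the normal pressure relieving interventions such as repositioning and other methods". That is a preventive instruction. It is not evidence that substitution will occur.

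**Comparing sheepskin cost between arms.** A reader might also infer that the plan compares a cost that is zero by design in controls. The protocol does not say so. Research question 2 asks what applying the sheepskin costs, question 3 asks for treatment cost in the two groups, and question 4 brings costs and effects together.

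**Assumed minutes and full stays.** Minutes per change are assumed. Inclusion requires only an expected stay of more than a week, patients may stop the sheepskin, and some changes may be done during ordinary bed care. All of this can shrink the figure, but it does not reverse its direction.

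**Conclusion.** The point holds in a limited form. The stated cost items are incomplete for the stated perspective. Nursing time to fit and change sheepskins is omitted while nurse time for ulcer treatment is counted, so the incremental cost is understated in the sheepskin's favour. The direction is clear as long as a change takes any extra staff time.

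The documents do not allow the size to be fixed. About 150 changes per ulcer averted follows from the protocol's own schedule and planned effect, for one skin location and patients who complete 30 days. The 2.5 to 25 nurse-hours rest on an assumed 1 to 10 minutes per change.

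It is tempting to conclude that the whole cost-effectiveness result would be wrong. The documents do not support that. One component is biased by an unknown amount. For other prevention, what is lacking is a stated costing, since use is recorded, and this matters only if use differs between arms.

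**What to change.** 1. Add staff time for fitting and changing to the sheepskin cost: number of changes × minutes per change (one-off estimate on a sample of wards, net of ordinary bed care) × wage rate. Vary the minutes in a sensitivity analysis. If the item is to stay out, state why and show the result with it included.
2. Attach unit costs to the support surfaces and devices already recorded in both arms.
3. Handle repositioning time only as a sensitivity analysis with assumed minutes. The checklist records whether it was applied, not how often or for how long, so staff time cannot be derived from it.
4. Base cost-effectiveness on the between-arm difference in net cost per patient (sheepskin purchase, washing and change time, priced other prevention, ulcer treatment), reported with its uncertainty.
5. Vary the number of washes per sheepskin up to the stated limit of 60, which the Background gives as a maximum. If each change means one wash, 15 changes use 15/60 = 0.25 of a sheepskin's life per location at 60 washes, and 15/30 = 0.5 at an assumed 30. Using 60 throughout would itself favour the sheepskin.

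The cost is a small timing exercise, a list of unit prices and some extra analysis. No new patient-level form is needed, and the incidence comparison and sample size are untouched.

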### Data-analysis

First of all the primary outcomes will be analyzed using descriptive methods.

Statistical testing of differences in incidence and prevalence between experimental and control groups will be conducted by a two-sided Chi-square test. In addition, differences in number of pressure ulcer free days will be tested with a two-sided t-test for independent samples; and differences in onset of pressure ulcers will be analyzed with Kaplan Meier curves. All analyses will be controlled for influencing factors. Moreover, a multi level analysis will be performed because of the fact that data are gathered from several organizations and nursing wards.

Both intention-to-treat-analysis and per-protocol-analysis will be carried out.

The economic data about costs will be used in a model approach to show the economic consequences on a higher level. The aim is to develop a model that can show the consequences of implementing improved pressure ulcer care for an average nursing home and/or the national level.

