**Methods/Design:**

In a multi-centre randomised controlled trial 750 patients admitted for a primarily somatic reason to one of the five participating nursing homes, and not having pressure ulcers on the sacrum at admission, will be randomized to either usual care only or usual care plus the use of the Australian Medical Sheepskin as an overlay on the mattress.

Outcome measures are: incidence of sacral pressure ulcers in the first month after admission; sacrum pressure ulcer free days; costs; patient comfort; and ease of use. The skin of all the patients will be observed once a day from admission on for 30 days. Patient characteristics and pressure risk scores are assessed at admission and at day 30 after it.

Additional to the empirical phase, systematic reviews will be performed in order to obtain data for economic weighting and modelling.

The protocol is registered in the Controlled Trial Register as ISRCTN17553857.

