### Participants

The study population will concern patients newly admitted for a primarily somatic condition to one of the five participating nursing homes. Only patients who are free of sacral pressure ulcers on admission will be included. Further inclusion criteria are: adult; not having darkly pigmented skin (because of difficulty in diagnosing grade 1 pressure ulcer); having an expected stay of more than one week; and consenting to the research.

For practical reasons and because 74% of nursing home patients in the Netherlands are at risk for pressure ulcer development [4], we have chosen to involve all patients, and not only patients at risk.

The patients will be recruited from 5 different Dutch nursing home care groups (Amstelring, Florence, Frankeland, Sutfene, Swinhove) involving seven different geographical locations and 18 wards. The selection of the nursing homes was made on the basis of the customer list of the laundry company that we contacted, and which is able to do the washing and drying of the sheepskin, according to the Australian Standard [35].

Inclusion of patients started on May 1^st ^2007 and will proceed until the targeted number of patients is reached, for a maximum of 1.5 years. It is expected that enough patients will be admitted during this period to reach the necessary number as was calculated by power-analysis.

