With regard to treatment adherence, patients from the intervention group are asked only to keep the sheepskin in their bed for 30 days. No other action is required from patients other than actions that are also asked in the control group. However it remains possible that some patients after a few days will refuse the sheepskin (e.g. because of itching, not feeling comfortable, too hot, or other reason): in these cases the use of the Australian Medical Sheepskin will be stopped without persuading patients to continue, but they will be asked if the daily skin observations can be continued. Records will be kept of patients that have discontinued the use of the Australian Medical Sheepskin (including reasons to stop), and they will be analyzed in the group they were randomized, according to intention to treat analysis principles.

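### The t-test on raw ulcer-free days mixes ulcer prevention with length of stay, because patients expected to stay just over a week are enrolled for a 30-day outcome

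*Protocol article*

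**What the plan says.** All places are in the protocol article.

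- **Participants:** eligibility requires "having an expected stay of more than one week".
- **Outcomes:** the effectiveness primary is "the incidence of sacral pressure ulcers in the first 30 days after admissions".
- **Abstract, Methods/Design:** "The skin of all the patients will be observed once a day from admission on for 30 days". Ulcer-free days are listed there among the outcome measures, but they are in neither the primary nor the secondary list under Outcomes.
- **Data-analysis:** incidence is compared between arms by chi-square. For the day count, "differences in number of pressure ulcer free days will be tested with a two-sided t-test for independent samples". Time of onset is left to Kaplan-Meier curves, for which no between-arm test is named. Covariate-controlled and multilevel analyses are planned, on both an intention-to-treat and a per-protocol basis.
- **Discussion:** patients who give up the sheepskin are analysed as randomised, and "they will be asked if the daily skin observations can be continued".
- **Ethical considerations:** any patient may stop participating at any time.
- **Sample size calculation:** about 5% drop-out is allowed for. The example given is inability to consent, not discharge or death.

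**The concern.** An expected stay just over one week satisfies eligibility, while the outcome runs to day 30. Some patients can be expected to go home or die before the window closes, so the number of days on which an ulcer could be seen varies between patients.

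An independent-samples t-test on a raw count of ulcer-free days has no means of separating a day lost to an ulcer from a day lost to discharge. Early leaving that is equal in both arms adds noise and shrinks the contrast. Leaving that differs between arms shifts the mean even when the sheepskin does nothing. The arm that loses more patients early looks worse on ulcer-free days and, if leavers are scored on what was seen, slightly better on incidence. Two analyses in the same paragraph could then point in opposite directions for a reason unrelated to ulcers.

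**Working it through.** **The plan's own figure.** Inputs from Sample size calculation: 28% versus 18%, two-sided alpha 0.05, 375 per arm. With mean proportion 0.23:

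n per arm = [1.96·√(2·0.23·0.77) + 0.8416·√(0.28·0.72 + 0.18·0.82)]² / 0.10² = (1.1665 + 0.4973)² / 0.01 = 277.

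So 554 patients give 80% power, and 375 per arm gives 90.4%. The stated power of at least 80% is true, with room to spare for the chi-square test.

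**Assumptions for follow-up (none are in the documents).** Constant ulcer hazard h = −ln(1−p)/30. A fraction f of patients leaves at a time uniform over days 8 to 30. Ulcer-free days = the earliest of onset, exit and day 30, with no healing. Leavers enter the chi-square on their observed status.

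**t-test, no leaving.** h = 0.01095 (28%) and 0.00662 (18%). The mean is p/h: 25.57 and 27.21 days, difference 1.64. The second moment is 2[1 − e^(−30h)(1+30h)]/h², which gives SDs of 8.45 and 6.99.

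SE = √[(8.45² + 6.99²)/375] = 0.566. Power ≈ Φ(1.64/0.566 − 1.96) = Φ(0.94) = 82.6%.

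**t-test, 30% leaving in both arms.** Simulated means 22.99 and 24.36 (difference 1.37), SDs 9.01 and 8.23. SE = √[(9.01² + 8.23²)/375] = 0.630. Power ≈ Φ(1.37/0.630 − 1.96) = Φ(0.21) = 58.5%.

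**t-test, no true effect (23% in both arms), leaving 25% control and 35% sheepskin.** Means 24.14 and 23.24, SDs 8.57 and 8.69. SE = 0.630. Rejection ≈ Φ(1.96 subtracted from 0.90/0.630) = Φ(−0.53) ≈ 30%, in the direction of harm from the sheepskin.

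**Both tests side by side (simulation, 375 per arm):**

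| Scenario | t-test | chi-square |
|---|---|---|
| True effect, 0% leaving | 82–83% | 91% |
| True effect, 15% in both arms | 70% | 89% |
| True effect, 30% in both arms | 58–59% | 86–87% |
| True effect, 45% in both arms | 49–50% | about 85% |
| True effect, 10% control, 20% sheepskin | 17% | 93% |
| No effect, 25% vs 30% | 11–12% | 5–6% |
| No effect, 25% vs 35% | 29–31% | 5.7% |

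Ranges are the spread over repeated runs; the lower end is quoted for the t-test in the summary and conclusion. At 30% equal leaving, recorded incidence is about 25.2% versus 16.1%.

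**Opposite directions.** With 28% in both arms, no effect, exits from day 7, and leaving of 20% control and 40% sheepskin: incidence is 26.0% versus 24.0% (2.0 points for the sheepskin after rounding), while ulcer-free days are 23.77 versus 21.96 (1.8 days against it).

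**Excluding leavers instead.** Chi-square power is 83.1%, 77.8% and 71.4% when 20%, 30% and 40% are excluded.

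**Stopped observation in the sheepskin arm only (Discussion).** No true effect, 28% in both arms, a fraction q unobserved after day 5. Recorded incidence = (1−q)·0.28 + q·(1−e^(−5·0.01095)), where the last bracket is 0.0533.

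- q = 15%: 0.238 + 0.008 = 24.6%, a false benefit of 3.4 points; a significant benefit appears in 18% of trials (nominal 2.5%).
- q = 5%: 0.266 + 0.0027 = 26.9%, 1.1 points; about 5%.
- q = 2%: 0.5 points; about 3.4%.

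**The case against.** **The article states no scoring rule.** A reader might infer that the plan counts early leavers as ulcer-free in the chi-square and as lost days in the t-test. The text does not say so. Leavers could be excluded or imputed, and such detail commonly sits in a full protocol or analysis plan that is not shown. This stands: the absence of a rule is not the point. What remains is the stated choice of a raw day count and a t-test.

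**The large figures belong to a lesser outcome.** Ulcer-free days appear in the abstract and as an additional analysis, not in the Outcomes lists. The trial is powered on incidence, and the chi-square holds up under the same scenarios. This also stands. A reader might conclude that the main effectiveness comparison is invalid; the calculations do not support that.

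**Kaplan-Meier curves are already planned.** They can censor discharge and stopped observation, so the plan does not ignore timing. The answer is partial: no comparative test is named for the curves, and death is a competing event.

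**The leaving rates are assumed.** An expected stay above one week is an eligibility floor, not a distribution of stays, and the only loss figure given is about 5%. Days after healing might also count, since the daily checklist records presence or absence of an ulcer. The size is therefore uncertain, but the mixing of stay and prevention is not.

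**Stopping the sheepskin.** A reader might infer that the Discussion builds in a bias favouring the sheepskin. The passage in fact tries to retain observation, and withdrawal is open to both arms. Only sheepskin patients meet this extra question, so a route exists, but nothing in the documents quantifies it.

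**Conclusion.** The point holds for the ulcer-free-days analysis, at moderate severity. As written, the t-test compares a quantity that depends on how long patients stay. If days are counted while observed, its power falls from about 82% to about 58% at equal 30% leaving, and its false-positive rate reaches about 29% at 25% versus 35% leaving with no effect. These figures assume leaving rates that the documents do not give, a constant hazard and no healing.

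The chi-square test on incidence is little affected by those patterns: power about 87%, rejection about 6%. It does ignore unequal follow-up, and it would be biased if the unobserved patients differ between arms. Whether that happens cannot be judged from the documents.

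**What to change.** 1. Replace the t-test on raw ulcer-free days by a comparison of restricted mean ulcer-free time to day 30, or by ulcer-free days per day observed.
2. Add a between-arm test to the planned Kaplan-Meier analysis: log-rank or Cox, adjusted for admission Braden score and ward. Censor at discharge and treat death as a competing event.
3. Report the 30-day risk difference from cumulative incidence beside the chi-square result.
4. State in the Discussion and the ward instruction that giving up the sheepskin does not in itself end daily skin observation. The right to withdraw under Ethical considerations is unchanged.

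The cost is analysis wording and one sentence of instruction. Daily observations already supply onset dates, so no new outcome data are needed beyond the dates of discharge and death. The downside is that the analysis must state its assumption that leaving is not informative about ulcer risk. The change should be made before the data are analysed.
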